### Follow-up

Participants in both groups will receive a phone call from the research fellow on day 5 and day 10 to check on progress and answer any questions. They will meet the clinician at the end of the 2-week trial period for a consultation guided by the data that have been collected. The follow-up appointment will be arranged during the baseline meeting, at a time convenient to participants, and will take place in a clinic at the hospital.

In the intervention group, the clinician reviewing each patient will receive reports with relevant information and management suggestions from the PD_Manager software. In the control group, the content of the patient symptom diaries will be reviewed. If data from either PD_Manager or the symptom diary indicate that management changes are required or referrals to other therapists (such as speech and language therapist, dietician, occupational therapist, physiotherapist) would be beneficial, this will be implemented.

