### Acceptability outcomes

Assessment of acceptability for patients and carers will be undertaken at the end of the 14-day intervention period immediately after the feedback consultation with the clinician. A private room in the clinic will be identified for this purpose. Views will be collected by interview. Those in the intervention group will be asked about the following: how comfortable the devices were and how easy they were to use (determined with the same wearability and usability questions used in earlier testing of devices [15]; how useful the feedback they received from PD_Manager was; their views on communications with their neurologist regarding the PD_Manager outputs. The usefulness of the education section will also be assessed. A separate questionnaire will be used for participants in the control group to gather their views about the ease, burden and usefulness of the symptom diary. Questionnaires can be obtained from the corresponding author.

Back end data from the PD_Manager system will be provided to the researchers to enable an analysis of compliance with use of the devices by members of the intervention group. These data will be used to indicate how much the patients/carers valued using the devices.

Face-to-face interviews will be conducted with each clinician to explore their views about the relative usability and acceptability of PD_Manager and the symptom diary, and the value they perceive they provided in generating information for clinical decision making. Feedback will be sought by means of a semi-structured interview schedule on perceived usefulness to patients, carers and professionals, and adaptability to usual working schedules. The treating clinicians will be asked to comment on the ease of interpreting the data generated by the devices and the symptom diary and the ease of using this data in changing the treatment and care management of participants, as well as their views on this means of communicating with participants. The interview schedule can be obtained from the corresponding author.

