### Analysis

Reporting of results will follow Consolidated Standards of Reporting Trials (CONSORT) extension guidelines for randomised pilot and feasibility studies [25]. Data relating to individual participants will be recorded using unique study identifiers to maintain confidentiality. Research data will be analysed in each country and merged for comparison purposes. Data relating to quantitative variables (baseline characteristics of participants, acceptability and usability outcomes at follow-up) will be entered into Statistical Package for Social Sciences (SPSS) version 24 (IBM SPSS Statistics for Windows, version 24.0, IBM Corporation, Armonk, NY, USA) and analysed with simple frequencies; the intervention and control groups will be compared using appropriate statistical approaches, depending on the nature of the data. In accordance with the pilot nature of the study, the analysis will be non-confirmatory. Data from quality of life and other health outcomes will be inspected for potential use in any future effectiveness trials. Responses to open questions relating to participants’ views will be subject to narrative review. Two independent researchers will read and re-read comments and agree on themes within the data. The information generated by the PD_Manager devices will be analysed by the partners who developed each device.

We expect most participants to complete the trial, since the follow-up lasts only 2 weeks and ends with a consultation with a neurologist, that is in addition to their usual care. However, it is possible that a participant will be unable to complete or may wish to withdraw from the study, in which case their baseline data will be ignored. Another issue is that participants in the intervention group may not use the technology. We will know this from the automatic collection of data, and we will investigate reasons in the follow-up interview. Similarly, participants in the control group may not complete the diary, in which case we will similarly explore their reasons.

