The pilot study has been designed to avoid standard risks of bias wherever possible. Participants will be randomised to the intervention and control groups to protect against selection bias, and care has been taken to ensure both groups receive the same attention at all stages of the study. Attrition or non-compliance (with devices or symptom diaries) do not constitute an issue but rather are actions of interest in our analysis of acceptability. However, the nature of the intervention is such that clinicians cannot be blinded to the group allocations. Potential does exist for selective outcome reporting. Hence, we are gathering information on attitudes to technology at baseline from participants, carers and clinicians.

The pilot study will not evaluate effectiveness and cost effectiveness of the PD_Manager system, although such a trial may be warranted if feedback from this pilot is positive. Outcome measures that may be used in an effectiveness trial are being tested within the pilot, and the findings will provide a basis for sample size calculation for a definitive trial. Preliminary cost estimates will also be computed in the pilot study to provide initial indications about the value of gathering further evidence from a larger trial.

Data security and confidentiality are major issues in trials of this sort. Data Protection Directive 95/46/EC, on the protection of individuals with regard to the processing of personal data and on the free movement of such data, will be strictly followed. Data from devices will be transferred (as described earlier) and stored in a web-based cloud database (NoSQL Database -3Dnet) in anonymised and encrypted format as employed by Apple for iPhones (a FiWare cloud-based process). The servers storing the information in the cloud platform are based on Biotronics 3D’s 3DnetMedical platform in the UK in an ISO27001-accredited data centre located in London. They are operated in accordance with the Data Protection Act. No third parties can access data either from the devices or during transmission. Access to the database will be strictly controlled and will only be shared with researchers on the PD_Manager project. Administrators of the web-based cloud database will not have access to data. The full data management policy of the cloud administrators is available from the corresponding author.

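### Patient and carer views, and reasons for stopping, are gathered only at the day-14 clinic interview, so interview-based acceptability describes attenders

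*Protocol article*

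**What the plan says.** The section on acceptability outcomes sets one time and place for patient and carer views: "Assessment of acceptability for patients and carers will be undertaken at the end of the 14-day intervention period immediately after the feedback consultation". The mode is fixed as well: "Views will be collected by interview", in a private room at the clinic. Table 1 lists these interviews only in the post-intervention column.

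The Analysis section takes up non-use. For the intervention arm it says: "We will know this from the automatic collection of data, and we will investigate reasons in the follow-up interview". For the control arm, "participants in the control group may not complete the diary, in which case we will similarly explore their reasons". The same section allows that a participant may be unable to finish or may withdraw. The only provision stated for that case is that the person's baseline data are set aside.

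Under Follow-up, both arms receive a "phone call from the research fellow on day 5 and day 10 to check on progress and answer any questions". In the intervention arm, back-end compliance data are also supplied to the researchers: "These data will be used to indicate how much the patients/carers valued using the devices". The Discussion then says: "Attrition or non-compliance (with devices or symptom diaries) do not constitute an issue but rather are actions of interest in our analysis of acceptability".

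**The concern.** Acceptability is a research question, the aim of the pilot, and one of the consequences in the economic comparison. The dyads that found a method least tolerable are plausibly over-represented among those who withdraw or stay away. As the article is written, such a dyad is never asked for its views or its reason for leaving.

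The Discussion treats attrition as information about acceptability. A departure carries that information only if its reason is known. Without the reason, a dyad that rejects the wristband cannot be told apart from one that falls ill.

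Two results are at stake. Within an arm, a summary based on the interviews may be too favourable. Between arms, the comparison may be distorted if attendance differs. That is plausible when one group records its motor state every 30 minutes and the other wears sensors around the clock. The time patients and carers spend on either method also comes from questionnaires given at follow-up, so it is lost for the same people.

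**Working it through.** The point is mainly structural, so the first step follows each type of dyad through the stated procedures.

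| Dyad | Self-reported views | Reason for stopping | Other acceptability data |
|---|---|---|---|
| Uses the method, attends | Yes, day-14 interview | Not applicable | Back-end usage (PD_Manager arm) |
| Stops, still attends | Yes, day-14 interview | Yes, but late: a stop on day 3 is discussed 14 − 3 = 11 days afterwards | Back-end usage (PD_Manager arm) |
| Withdraws or does not attend, PD_Manager arm | No route stated | No route stated | Smartphone and wristband data, sent automatically; insole data wait for download by the researcher at the end of follow-up |
| Withdraws or does not attend, control arm | No route stated | No route stated | None described |

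For those who withdraw, baseline attitudes to technology and stated preference for either method could have described who left. The Analysis section sets these aside.

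The only relevant figures in the article are the numbers recruited. The site quotas give 110 + 50 + 20 + 20 = 200, and 1:1 allocation gives 200 / 2 = 100 per arm, in agreement with the sample size section. No withdrawal rate, non-attendance rate or expected favourable share is stated.

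The possible size can therefore only be bounded under assumptions. Let p be the favourable share among attenders and d the share who do not attend. Over all randomised in an arm:

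- lower bound (no non-attender favourable) = p(1 − d)
- upper bound (every non-attender favourable) = p(1 − d) + d
- width = d

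With p = 80% (assumed):

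| d (assumed) | Lower | Upper |
|---|---|---|
| 5% | 0.80 × 0.95 = 76% | 76 + 5 = 81% |
| 10% | 0.80 × 0.90 = 72% | 72 + 10 = 82% |
| 20% | 0.80 × 0.80 = 64% | 64 + 20 = 84% |

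For the arm comparison, assume 80% favourable among attenders in both arms, so the observed difference is 0. Count all non-attenders as unfavourable:

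- 10% non-attendance with PD_Manager, 5% with the diary: 72 − 76 = −4 percentage points
- 20% with PD_Manager, 5% with the diary: 64 − 76 = −12 percentage points

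The sign reverses if the diary arm loses more. These calculations also assume a common favourable/unfavourable item in both arms. The article does not define one and describes a separate questionnaire for each group.

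**The case against.** A reader might infer that every acceptability outcome hangs on the day-14 visit and that the results describe completers only. The documents do not support either statement. Back-end compliance data are named as an indicator of how far the devices were valued, and the smartphone and wristband part arrives without attendance. Clinicians' views come from their own interviews. Participants who stop using a device or diary but still attend are to be asked why, so the interviewed group is attenders, including non-users.

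It can also be said that the sentence in "We will know this from the automatic collection of data, and we will investigate reasons in the follow-up interview" concerns non-use rather than withdrawal; that a condensed article need not describe call forms or exit procedures; that the article does not say that nothing is recorded at the calls; and that most participants are expected to complete two weeks that end with an additional neurologist consultation. Some interview items, such as the usefulness of the feedback, make sense only after the consultation. A person may also leave for reasons unrelated to the method, so an upward bias is plausible but not certain.

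Most of this stands, and it limits the point. It does not remove it. The article positively fixes one collection point for views and reasons, states what happens to the data of withdrawals, and separately gives attrition a role in the acceptability analysis. Those three statements do not fit together. An analysis plan cannot recover answers that were never sought.

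**Conclusion.** The point holds for interview-based patient and carer acceptability and for the reasons for stopping. Both have one stated collection point, and a dyad that withdraws or does not attend supplies neither. The back-end data soften the gap in the PD_Manager arm by showing use, though not reasons. For control participants who do not attend, no counterpart is described, so the gap is uneven between arms.

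The size cannot be derived from the article. The uncertainty in each arm's share equals its non-attendance rate, and the percentages above are illustrations. If non-attendance proves very low, the effect is small. In a non-confirmatory pilot this is a worthwhile, inexpensive improvement to the trial's main aim, and not a flaw that invalidates the design.

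**What to change.** 1. At the existing day-5 and day-10 calls, record the same three items in both arms: whether the device or diary is still in use, the date of last use, and the main reason for stopping.
2. Offer dyads that withdraw or will not attend a short phone exit interview, if they agree. Limit it to what they can answer (comfort, ease, burden, reason for stopping) and leave out items on the consultation or feedback.
3. Keep withdrawals in the report. Give the number and reasons for stopping by arm over all randomised dyads. Beside the attender result, show a sensitivity summary that counts method-related stopping as not acceptable. This requires a definition of method-related stopping and of a favourable response, both set before the data are examined.
4. Reconcile the Analysis statement on the baseline data of withdrawals with the role that the Discussion gives to attrition.

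The cost is a short form for calls already planned, slightly longer calls, and a brief phone interview for those who leave. Some who withdraw will decline, so the gap will narrow but not close.

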### Sample size calculation

A formal sample size calculation is not normally required for a pilot study [26–29]. Authors have suggested various figures ranging from 20 to 70 participants [26, 29–32]. The *n* = 20 value for number of subjects who will be included in England and Greece is at the lower end of this range, but there will be a total of 200 people with Parkinson’s across the three countries, 100 of whom will test the PD_Manager system. The sample size of 200 for the three countries was selected based on complexities around the technologies involved, the desire to compare men and women and different ages and the desire to capture possible cross-country setting variations. The findings from the pilot study will be used to inform the calculation of a sample size for a future larger scale trial.

### Economic evaluation

An economic analysis embedded in the trial will compare the PD_Manager intervention with the symptom diary with respect to costs and acceptability and usability outcomes in a cost-consequences framework [33]. The cost of providing, maintaining and insuring the PD_Manager devices, access to the cloud programme and the data infrastructure will be obtained from the manufacturers and averaged over the expected number of users. The amount of provider time spent in training patients and carers, troubleshooting and in interpreting feedback for both groups will be gathered through observation and interview and valued using nationally validated unit costs [34]. The time patients and carers report spending in using either the PD_Manager devices or the symptom diaries will be gathered from the questionnaires administered at follow-up. The various elements of costs and consequences for patients, carers and clinicians will be presented in a disaggregated form in a descriptive table. Reporting will follow Consolidated Health Economic Evaluation Reporting Standards (CHEERS) [35].

## Discussion

When testing of the PD_Manager system is complete and a final version becomes available for routine use in clinical practice, it is expected to be used to assess people with Parkinson’s with symptoms that are hard to manage and in circumstances where a clinician wants more information than is provided by patient/carer self-report to guide medication and management planning. This pilot study represents a relatively early stage in the PD_Manager development process, to test acceptability and utility of the system from patient, carer and clinician perspectives. The people with Parkinson’s who are recruited to the trial may not have symptoms that fit the description of ‘hard to manage’ and may, in the opinion of the recruiting doctors, already be optimally managed. However, their opinions about the acceptability and potential usefulness of the PD_Manager system will still be valuable. All participants will be reimbursed for all reasonable travel and other out-of-pocket costs that they incur in order to take part in the research.

The products that constitute the PD_Manager system in this trial have previously been tested by their respective manufacturers and shown to be in conformity with relevant directives of the European Commission including health, safety and environmental protection (i.e. they hold CE (Conformité Européene/European Conformity) certificates). The PD_Manager project also tested the devices for wearability, possible discomfort and safety as part of earlier work packages [15]. The participants in these earlier studies were carefully selected to represent the disease characteristics of the target group. Given the cost and complexity of the system, devices are reused for multiple patients, and cleaning instructions provided by the manufacturer are scrupulously followed to prevent cross infection. None of the devices were found to pose any risks or significant discomfort to the participants [15].

The pilot study has been designed to avoid standard risks of bias wherever possible. Participants will be randomised to the intervention and control groups to protect against selection bias, and care has been taken to ensure both groups receive the same attention at all stages of the study. Attrition or non-compliance (with devices or symptom diaries) do not constitute an issue but rather are actions of interest in our analysis of acceptability. However, the nature of the intervention is such that clinicians cannot be blinded to the group allocations. Potential does exist for selective outcome reporting. Hence, we are gathering information on attitudes to technology at baseline from participants, carers and clinicians.

The pilot study will not evaluate effectiveness and cost effectiveness of the PD_Manager system, although such a trial may be warranted if feedback from this pilot is positive. Outcome measures that may be used in an effectiveness trial are being tested within the pilot, and the findings will provide a basis for sample size calculation for a definitive trial. Preliminary cost estimates will also be computed in the pilot study to provide initial indications about the value of gathering further evidence from a larger trial.

Data security and confidentiality are major issues in trials of this sort. Data Protection Directive 95/46/EC, on the protection of individuals with regard to the processing of personal data and on the free movement of such data, will be strictly followed. Data from devices will be transferred (as described earlier) and stored in a web-based cloud database (NoSQL Database -3Dnet) in anonymised and encrypted format as employed by Apple for iPhones (a FiWare cloud-based process). The servers storing the information in the cloud platform are based on Biotronics 3D’s 3DnetMedical platform in the UK in an ISO27001-accredited data centre located in London. They are operated in accordance with the Data Protection Act. No third parties can access data either from the devices or during transmission. Access to the database will be strictly controlled and will only be shared with researchers on the PD_Manager project. Administrators of the web-based cloud database will not have access to data. The full data management policy of the cloud administrators is available from the corresponding author.

Data collected from participants by researchers will be recorded by unique study identification number. No names or personal information will be stored on or with these forms. Information will be kept in locked filing cabinets and password-protected computers in restricted access rooms at the study sites. Data will be shared only with researchers in the PD_Manager project. All data gathered will be the property of the PD_Manager consortium, and access by external researchers will only be authorised by the PD_Manager board. An embargo will be present until the end of the project with respect to access for researchers external to the study group.

Results of this pilot study will be presented to the funders as a report. The research team will write papers for publication in journals and make conference presentations to influence the development of future treatment and services for people with Parkinson’s. A summary of the study results will be available from the project website (http://www.parkinson-manager.eu/).

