### Aims and objectives

The aim of the pilot study is to explore the acceptability and utility of the PD_Manager system to patients, carers and clinicians, in a community setting, compared to a symptom diary, to inform further developments and the design of a larger clinical trial which will assess effectiveness (patient and carer health outcomes).

The specific objectives of the pilot study are to:Assess patient perspectives of the PD_Manager mHealth platform regarding comfort, acceptability, ease of use and understanding of Parkinson’sAssess the views of clinicians about the PD_Manager mHealth platform, i.e. usefulness of the information provided for decision making regarding patient management; acceptability in clinical practice; confidence in reliability of the informationExplore the resource implications and costs of the PD_Manager system for patients/carers and providers and consider these in the light of potential outcome differences, compared to the symptom diary, in a cost-consequences framework.

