#### Randomisation

Following baseline data collection, participants will be randomised to receive either PD_Manager (the intervention) or to be in the control group (symptom diary/no PD_Manager). Randomisation will be 1:1, blocked and by quota within each country and will be conducted using sealed envelopes prepared by an independent statistician. Given the higher incidence for Parkinson’s in men than in women, its increasing prevalence with age and a concern that younger people may be more accepting of technology than older people, the objective is to recruit 40% women and to have one half of each gender be under 70 years of age.

Participants will be informed of their group allocation immediately, and a researcher will provide the PD_Manager devices (intervention group) or the symptom diary (control group) and give full information about how they are to be used over the following 2-week trial period. Blinding of participants, researchers and clinicians will not be possible given the nature of the intervention.

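### Acceptability is gathered only from people who reach the closing interview, and withdrawers' baseline data are discarded, so the acceptability share is likely to be too favourable

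*Protocol article*

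**What the plan says.** Four places in the protocol article bear on this.

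- **Aims and objectives.** The pilot explores acceptability and utility against a symptom diary, "to inform further developments and the design of a larger clinical trial which will assess effectiveness". Patient views are sought "regarding comfort, acceptability, ease of use and understanding of Parkinson"'s disease.
- **Acceptability outcomes.** Patients and carers are interviewed once, straight after the feedback consultation that closes the two weeks. Device back-end data are also used to analyse compliance in the intervention group.
- **Analysis.** Most participants are expected to complete. For someone who cannot, or who withdraws, the instruction is "in which case their baseline data will be ignored". Non-use of the devices is to be seen from the automatic data and explored in the follow-up interview. Reasons for an incomplete diary are to be explored similarly.
- **Discussion.** Attrition and non-compliance are described as being of interest for the acceptability analysis rather than as a problem. The same section says that a larger effectiveness trial "such a trial may be warranted if feedback from this pilot is positive".

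**The concern.** In a study of acceptability, stopping early is itself evidence. A person who gives up the wristband and insoles after a few days has told the team something that a satisfied completer has not. Under the procedures described, that person does not reach the interview and their baseline record is set aside, so they contribute neither to the numerator nor to the denominator of an acceptability share.

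Two things are at stake. First, the share of favourable answers is too high whenever withdrawers would have been less favourable than completers, and this is the figure the article links to a larger trial. Second, discarding baseline data removes the means of seeing who left. The article collects age, gender, preference for either method and attitudes to technology because it expects these to colour later views. Without withdrawers' records, nobody can tell whether older or more technology-averse participants dropped out.

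**Working it through.** **Inputs from the article.** The centre targets are 110 + 50 + 20 + 20 = 200. With 1:1 allocation, 200 / 2 = 100 are on PD_Manager, which agrees with the Sample size calculation section. No withdrawal rate or acceptability rate is given, so both are assumed below.

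**Who is covered by which procedure.**

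| Participant | Closing interview | Device back-end data | Baseline data |
|---|---|---|---|
| Completes and uses devices | yes | yes | kept |
| Attends but did not use devices | yes, asked for reasons | shows non-use | kept |
| Withdraws or cannot complete | no stated route | at most up to stopping | ignored |

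The safeguards cover the second row. The third row is the gap.

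**Formula.** Let n be the number randomised to PD_Manager, w the fraction who withdraw and f the number of completers who are favourable.

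- Completers-only share: f / [n(1 − w)]
- All-randomised share, withdrawers counted as not acceptable: f / n
- Difference: completers-only share × w

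**Illustration (assumed: n = 100, w = 0.15, f = 60).**

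- Completers only: 60 / 85 = 70.6%
- All randomised: 60 / 100 = 60.0%
- Difference: 0.706 × 0.15 = 10.6 percentage points

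For scale, the 95% half-width for 60% of 100 is 1.96 × √(0.6 × 0.4 / 100) = 9.6 points. In this illustration the choice of denominator moves the result by slightly more than sampling error does.

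**Range over the assumed withdrawal rate, completers-only share held at 70.6%.**

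| Withdrawal | All-randomised share | Difference |
|---|---|---|
| 5% | 0.706 × 0.95 = 67.1% | 3.5 points |
| 10% | 0.706 × 0.90 = 63.5% | 7.1 points |
| 15% | 0.706 × 0.85 = 60.0% | 10.6 points |
| 20% | 0.706 × 0.80 = 56.5% | 14.1 points |

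**How far the conservative count can err.** If k of the 15 withdrawers would have been favourable, the share among all randomised is (60 + k) / 100, which runs from 60% (k = 0) to 75% (k = 15). The completers-only 70.6% is too high whenever k is below 0.706 × 15 = 10.6, that is, 10 or fewer. It would be too low only if at least 11 of the 15 people who left had liked the system.

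**Between the arms.** If the diary arm had no withdrawals and 60 of 100 favourable answers, completers-only summaries would show 70.6% against 60.0%, although 60 people in each arm gave a favourable answer. The arms have separate questionnaires, so this shows only the direction in which unequal withdrawal works.

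**The case against.** The best defence is that the instruction concerns baseline data only. It does not say that withdrawers' device data or reasons are dropped from the acceptability analysis. The article also plans a compliance analysis, asks non-users why, commits to a reporting guideline for pilot trials, and expects few losses over two weeks that end with an additional neurologist consultation. All of this is fair, and low attrition would make the effect small. But the non-use enquiry takes place at the closing interview, which a withdrawer does not attend, and compliance data record wear, not opinion. No other route for withdrawers' views is described. The full protocol (version 4) is not shown and may contain one. Even so, the instruction printed in the article would still need to go.

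A reader might go further and treat "such a trial may be warranted if feedback from this pilot is positive" as a go/no-go rule so loose that the pilot cannot return a clear no. The article does not support that. The sentence is an aside in the Discussion, its wording is permissive, and plainly negative feedback would not satisfy it. The stated aim is to inform development and design, the analysis is declared non-confirmatory, and cost estimates are also meant "to provide initial indications about the value of gathering further evidence from a larger trial". A progression threshold is a detail that a journal article commonly leaves to the full protocol.

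A reader might also calculate the chance that at least one of many items looks good by luck, particularly since the Discussion concedes that "Potential does exist for selective outcome reporting". Such a calculation assumes that any single favourable item would count as overall success. The article states no such rule, and answers from the same users would be correlated.

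**Conclusion.** The concern holds in a limited form. The Analysis section's handling of withdrawers conflicts with the Discussion's statement that attrition belongs in the acceptability analysis, and it leaves the acceptability share resting on people who stayed. The bias is upward if withdrawers are less favourable than completers. That is plausible when the devices are a reason for leaving, but it cannot be verified from the article. The overstatement relative to the conservative count equals the completers-only share times the withdrawal fraction: 3.5 to 14.1 points for assumed withdrawal of 5% to 20% at a completers-only share of 71%, and negligible if almost everyone completes. The finding does not rest on the missing progression threshold, on multiplicity or on the lack of blinding, and it does not show that the pilot is unable to give a negative answer.

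**What to change.** 1. Delete the instruction to ignore the baseline data of people who withdraw or cannot complete. Report these data by arm alongside those of completers.
2. Keep all randomised participants in the denominator of the acceptability summaries.
3. In the main summary, count those who withdraw or never use the devices (or the diary, in the control arm) as not acceptable.
4. Show the completers-only figure and the withdrawal reasons alongside, so that readers can see how much depends on the choice.

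The baseline data are already collected and no extra participants are needed. Reasons would have to be asked for when someone stops. The planned calls on days 5 and 10 offer one existing point of contact. The price is a somewhat less favourable and conservative main figure, because some people will leave for reasons unrelated to the devices. The completers-only figure and the reasons let a reader judge that.

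Optionally, the team could name one lead acceptability item and a progression threshold before looking at follow-up data. This is a suggestion, not a correction, and the article gives no basis for any particular cut-off.
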